### Interim analyses {21b}

Not applicable. No interim analyses were planned.

### Methods for additional analyses (e.g., subgroup analyses) {20b}

Survey questions not listed as primary or secondary outcomes will be compared between the two study groups at each of the 7 days of follow-up. Subgroup analyses will be conducted by performing the same analyses as described above separately by sex and age (6–9 vs. 10–14, 15–17 years of age).

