### Sample size {14}

The sample size was calculated for the primary outcome of the child-reported overall pain score. We consider a 30% reduction in the pain NRS score as a minimal clinically meaningful reduction in pain. According to our previous publication on pain reduction of VR-PAT among pediatric patients 6–17 years of age who were treated at our outpatient burn clinic [19], the pooled standard deviation (SD) of the child-reported overall pain visual analog scale (VAS) score was estimated. Aiming at detecting a 30% reduction of the pain score in the VR-PAT group compared with the control group at any of the first 7 days of follow-up, and assuming the same SD on these days, we will need 89 subjects per group to achieve 80% power and a two-sided type-I error of 0.01 at each day using a two-sample *t*-test. The type-I error rate is adjusted by Bonferroni correction for multiple comparisons. Assuming a 10% dropout rate, we will need 99 subjects per group. Based on this calculation, we plan to *n* = 100 subjects per group (*n* = 200 subjects total).

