## Statistical methods

### Statistical methods for primary and secondary outcomes {20a}

#### Aim 1

In the primary analysis, the child-reported overall pain NRS score will be compared between the VR-PAT and control groups during each of the first 7 days of follow-up using a two-sample *t*-test. The *p* values will be adjusted by Bonferroni correction to account for multiple comparisons and then compared to the critical value of 0.05 to determine statistical significance. In the secondary analysis, child-reported worst pain score, parent-observed overall and worst pain scores, child engagement and experience with VR, caregiver report of VR use, and adverse effects related to engagement with VR will be compared between the two study groups using a two-sample *t*-test (for continuous variables) and chi-squared test (for categorical variables). To estimate the overall difference in the child-reported overall pain score between the two study groups over the 7 days of follow-up, a linear mixed effect model with random intercept accounting for the correlation among repeated measures of pain scores will be fit. The dependent variable of the model will be child-reported overall pain score. The independent variables of the model will contain the study group, time (follow-up days), and any potential confounders deemed unbalanced between the study groups. The coefficient of the study group is the estimated overall difference in the pain score. To further explore whether the trend of child-reported overall pain score over the 7 days differs between study groups, the same linear mixed effect model as above will be fit with the addition of interaction between the study group and time. The coefficient of the interaction term estimates the difference in the trend of pain scores over time.

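### Subgroup analysis is specified as separate reruns by sex and three age bands with no interaction term stated, so nothing planned estimates whether the VR-PAT effect differs between subgroups

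*Protocol article*

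**What the plan says.** The section on additional analyses {20b} gives the subgroup method in one sentence: "Subgroup analyses will be conducted by performing the same analyses as described above separately by sex and age". The age bands are "6–9 vs. 10–14, 15–17 years of age".

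The analyses referred to are in the statistical methods section {20a}. Child-reported overall pain is compared between arms "during each of the first 7 days of follow-up using a two-sample *t*-test". The p values are "adjusted by Bonferroni correction to account for multiple comparisons and then compared to the critical value of 0.05". The same section plans a linear mixed model for the overall 7-day difference between arms, and a second version "with the addition of interaction between the study group and time". That group-by-time term is the only interaction in the article, and it concerns the trend of pain over days. The article does not call the subgroup analyses exploratory and does not limit them to estimation.

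**The concern.** The question behind a subgroup analysis is whether the treatment effect differs between kinds of children. It is answered by the difference between subgroup effects, with its uncertainty. Rerunning the tests within each subgroup answers another question: whether the arms differ detectably in that subgroup alone. The answer depends heavily on how many children are in the subgroup.

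The stated method gives 5 subgroups × 7 days = 35 significance verdicts on the primary pain score, and no estimate of a between-subgroup difference. If one sex or age band reaches significance and another does not, it is easy to conclude that VR-PAT works only in the first. The article plans an implementation toolkit and foresees a rollout study across burn centers, and a false conclusion of that kind could misdirect both.

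**Working it through.** **Inputs from the sample size section {14}.** The design statement is "we will need 89 subjects per group to achieve 80% power and a two-sided type-I error of 0.01 at each day". The target is a 30% reduction, but the article gives neither the control mean nor the SD as a number. The 89 therefore cannot be rebuilt forwards. Solved backwards:

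- Normal approximation: d = √(2/89) × (2.576 + 0.842) = 0.512.
- Noncentral t: d = 0.517, used below.
- Dropout step: 89/0.9 = 98.9, so 99. This agrees with the plan, which then recruits 100 per arm.

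**Assumptions.** The true effect is 0.517 SD on every day in every child. Sexes split 50:50 and age bands in thirds. There are 89 (after dropout) to 100 children per arm. Correlation between days is 0.5 to 0.7. None of the splits or correlations is in the article.

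**Formulas.** For power p in each of two equal subgroups, they disagree with probability 2p(1 − p). For three equal bands with power q, they are not all alike with probability 1 − q³ − (1 − q)³.

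**Single day, two-sided 0.05/7 = 0.00714.**

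| Per arm | Power per sex | Sexes disagree | Power per age band | Bands not all alike |
|---|---|---|---|---|
| 89 | 38.2% | 2 × 0.382 × 0.618 = 47.2% | 22.3% | 52.1% |
| 100 (50 per sex, 33 per band) | 44.0% | 2 × 0.440 × 0.560 = 49.3% | 25.8% | 57.5% |

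Unequal splits do not help. With 89 per arm, a 70:30 sex split gives 53.8% and a 45/35/20 age split gives 54.0%. Using 0.01 per day, as in the sample size section, gives 48.9% and 57.8% with equal splits.

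**Any of the 7 days significant at 0.05/7 (simulation).** The sexes disagree in about 26–42% of trials over 89 to 100 per arm and correlation 0.5 to 0.7. With 89 per arm the age bands are not all alike in about 70–75%.

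**Overall 7-day difference.** The 7-day mean stands in for the mixed model, tested at an assumed 0.05. Averaging 7 equally correlated days multiplies the SD by √((1 + 6ρ)/7), which is 0.756 at ρ = 0.5 and 0.862 at ρ = 0.7. The effect becomes 0.517/0.756 = 0.684 or 0.517/0.862 = 0.600.

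| Per arm | ρ | Power per sex | Sexes disagree | Bands not all alike |
|---|---|---|---|---|
| 100 | 0.5 | 92% | 14% | 51% |
| 100 | 0.7 | 84% | 26% | 66% |
| 89 | 0.5 | 89% | 19% | 58% |
| 89 | 0.7 | 80% | 32% | 70% |

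**Sensitivity to the effect.** On a single day with 50 per arm per sex, the sexes disagree in 8% of trials at d = 0.2, 20% at 0.3, 19% at 0.8 and 3% at 1.0. For the age bands at 33 to 34 per arm the figure is about 65% at d = 0.8 and about 27% at 1.0.

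**Comparison with an interaction test.** With equal true effects, a test at 0.05 wrongly signals a difference in 5% of trials per factor. For two independent factors that is 1 − 0.95² = 9.75%.

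**Power of the interaction test for sex (89 per arm, 44.5 per arm per sex).** The standard error of the difference between two subgroup effects is √(4/44.5) = 0.300 SD. On a single day, a between-sex difference as large as the whole design effect gives 0.517/0.300 − 1.96 = −0.24, or about 41% power. Half that difference gives about 14%. On the 7-day mean, the full difference gives 0.684/0.300 − 1.96 = 0.32 (about 63%) at ρ = 0.5, and 0.600/0.300 − 1.96 = 0.04 (about 52%) at ρ = 0.7.

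**The case against.** A reader might infer that the investigators will judge subgroup differences by setting a significant result in one group against a non-significant one in another. The article does not say so. It states how the subgroup analyses are run and is silent on how they will be compared. Reporting results within subgroups is ordinary practice and not wrong in itself. This stands, and it is why the disagreement figures are conditional.

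The article is also a condensed account. A statistical analysis plan that is not shown could add an interaction test without contradicting this text. That weakens the point but does not remove it. The article does not leave the method open: it names one, and that method does not produce the quantity a subgroup analysis needs.

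Quoting only the single-day figure for sex would overstate the problem. Two subgroups of equal power can disagree at most 50% of the time, and the back-solved effect puts 47–49% close to that ceiling. The planned mixed model brings the figure for sex down to about 14–32%. This also stands. The age-band figure holds up better, at about 51–70%.

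Finally, these are additional analyses, and the proposed interaction test has low power. Both are true. Low power is a reason to report estimates as exploratory. It does not justify separate tests, which use the same data and do not address the difference.

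**Conclusion.** The point holds in this limited form. The article fixes a subgroup method that returns separate significance verdicts by sex and age band and no estimate of a difference in effect between them. If those verdicts are contrasted, equal effects will often look different. Across the analyses tried, that is about 14–49% of trials for sex and about 51–75% for the age bands, assuming equal splits and a common effect of 0.517 SD.

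The figures rest on the back-solved effect, the assumed splits and the assumed correlation between days. For sex they fall steeply at much smaller or larger effects. For the age bands they stay high at moderately larger effects before falling. The documents do not show that a false subgroup claim will be made, and the primary comparison of arms is not affected.

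**What to change.** In section {20b}, replace the separate reruns with group-by-sex and group-by-age terms in the linear mixed model already planned in section {20a}. Age may enter as the three bands or as a continuous variable. Report the interaction estimates with 95% CIs and p values as the test of whether the effect differs. Show within-subgroup estimates with CIs but no separate significance verdicts, and label all subgroup analyses exploratory. If the statistical analysis plan already does this, align the article's text with it.

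The cost is a wording change and two sets of model terms, with no new data. The drawback is the low power of the interaction tests, shown above: about 41% on a single day for a between-sex difference as large as the whole design effect. A non-significant interaction should therefore not be read as evidence that the effect is the same in all children.

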### Methods in analysis to handle protocol non-adherence and any statistical methods to handle missing data {20c}

The intention-to-treat principle will be used in the primary analysis, in that subjects will be analyzed according to their assigned study group regardless of whether they used the VR-PAT or in the control group during dressing changes. Subjects that drop out of the study will be excluded from analyses after their dropout date. As a sensitivity analysis, the missing pain scores due to dropout will be imputed by multiple imputations with chained equations, and two-sample *t*-tests will analyze the imputed dataset. For Aim 2, sensitivity analysis will be conducted by imputing missing scores due to dropout and then recalculating the mean scores and their 95% confidence intervals.

### Plans to give access to the full protocol, participant level data, and statistical code {31c}

Public access to the full protocol and statistical code is available upon reasonable request to the corresponding author. De-identified research data will be made available upon reasonable request to the Data Trust & Value Committee at Nationwide Children’s Hospital via e-mail at [contact].

## Oversight and monitoring

### Composition of the coordinating centre and trial steering committee {5d}

This trial will be overseen and coordinated by the contact PI, two site PIs, and a project manager. Each site has at least one study coordinator to assist with the screening, recruitment, consent, and data collection. The site PIs monitor the research activities at their respective institutions, while the project manager and the contact PI monitor research progress study-wide. The contact PI and project manager meet weekly to discuss the project, including recruitment updates, challenges, and any reported adverse events. The project manager has monthly meetings with the study coordinators and weekly emails with recruitment updates. The full study team meets quarterly. There is no specific steering committee for this study.

### Composition of the data monitoring committee, its role and reporting structure {21a}

The NCH IRB did not require a data monitoring committee (DMC) as this is a minimal-risk study. The contact PI and the site PIs will be responsible for all research aspects of this study, including ensuring informed consent/assent policies are followed, keeping the study IRB compliant, and monitoring the data quality. The contact PI and site PIs will review all adverse events (AEs) and serious adverse events (SAEs). They will also ensure all AEs, SAEs, and protocol deviations are reported to the IRB and sponsor as per institutional requirements.

### Adverse event reporting and harms {22}

Participants in the intervention group will be asked to report at each dressing change to answer the question, “Did the game make you feel not well? If yes, please explain.” Study coordinators will carefully review collected data for any adverse events reported during the study intervention and immediately report this information to the project manager. The PIs will determine how serious the event was, whether it was related, and if it was unexpected. All SAEs will be reported immediately to the sponsor and IRB. At recruitment, participants and caregivers will be informed of what simulator sickness symptoms to be aware of and advised that if they occur, children can remove the headset and continue the dressing change without it. They can then choose whether to try again at the next dressing change or to continue their week of wound care without the headset. All participants will also receive a direct phone number for a study coordinator at each site to report adverse events.

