### Criteria for discontinuing or modifying allocated interventions {11b}

VR intervention group participants will be advised to discontinue using the headset during a dressing change if it causes motion sickness, headaches, nausea, or dizziness. Participants are welcome to try using the headset again for the next change but have the option of continuing the dressing changes and surveys without it or withdrawing from the study. Any adverse events from participation will be noted and reported on the subject surveys.

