### Strategies to improve adherence to interventions {11c}

To improve study completion and participation, all subjects will receive a VR headset and an app download for their participation in the study. After returning the daily surveys, participants will receive $25 on a Greenphire ClinCard. Study team coordinators will encourage completion and adherence to the protocol by offering various options for follow-up. Surveys can be returned in person, by mail via a pre-paid envelope, or scanned and emailed to the coordinator. The study team will conduct calls before the follow-up appointment and up to three calls after to remind subjects to return surveys.

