#### Content and protocol for the intervention (VR) group

Participants in the intervention (VR-PAT) group are given a folder similar to the control group with daily surveys, with the addition of download instructions for the VR-PAT smartphone application and a VR headset best suited for the participating child. The child is asked to wear and play the approved VR game during the dressing change, and then both the child and caregiver are instructed to complete the daily surveys after wound care.

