#### VR-PAT child surveys (self-reported)

In addition to self-reporting anxiety STAI-CH survey questions prior to wound care and assessing their overall pain score (NRS, 0–10), children are asked about their experience with the VR game (degree of realism, fun, engagement, and satisfaction) and pain perception while playing the VR game (NRS, 0–10). Participants are also asked to report any simulator sickness associated with the VR game.

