### Plans to promote participant retention and complete follow-up {18b}

Based on our pilot study, we do anticipate losing some participants to follow-up. We will attempt to promote retention by emphasizing the importance of returning surveys after their week of home dressing changes at the time of recruitment. The recruiter will also ask the legal guardian for a phone number where they can receive reminder calls. Participants in the VR group will be asked to download the app at the time of recruitment; however, if they choose not to, they may download it at home and are provided with contact information for the research team and receive a check-in phone call on the next business day following recruitment to ensure there were no technological issues. All participants will receive a reminder call before their next clinic appointment (or at the 7-day mark if they are not returning to the clinic). Additional reminder calls will be made once per week for up to 3 weeks to encourage the return of surveys. We will also allow participants to return surveys in person at a clinic appointment, by taking a photo and emailing them to an email address created specifically for this project, or by mailing them in a provided prepaid, self-addressed envelope. Participants who return surveys, thus completing all study procedures, will receive an incentive of $25 on a Greenphire ClinCard.

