### Confidentiality {27}

Prior to enrollment, screening spreadsheets and other electronic databases to access patient charts will be kept in a secure file folder on password-protected computers in the Research Institute at NCH and at Parkland Health. Only researchers on the IRB will have access to the secure folder where the file is located.

Eligible subject information will be entered in a locked research office on a hospital-approved password-protected computer. Enrolled subjects will be assigned a study ID number. The PI and limited trained research staff will maintain all components of the research record containing participants’ identifying information.

Hard copies and information collected during study enrollment are kept in a secure locked file cabinet in a locked office, with only study staff having access. Publication will not identify subjects or contain information leading to identification. The study team has no plans to contact the subjects after their study participation or to share PHI with anyone outside the study team.

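### Solicited adverse event data arrive only with take-home surveys returned after the week of headset use; asking about sickness on calls already planned would give earlier and more complete harms data

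*Protocol article*

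**What the plan says.** All references are to the protocol article.

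- **Where events are recorded.** Criteria for discontinuing or modifying allocated interventions {11b}: "Any adverse events from participation will be noted and reported on the subject surveys". The same section allows a child who stops the headset because of symptoms to try it again next time, to carry on with dressing changes and surveys without it, or to leave the study.
- **Form of the surveys.** "Participants in the intervention (VR-PAT) group are given a folder similar to the control group with daily surveys", according to the section on the intervention group. On the VR child survey, "Participants are also asked to report any simulator sickness associated with the VR game". Adverse event reporting and harms {22} adds an open question at each dressing change on whether the game made the child feel unwell.
- **Return.** Strategies to improve adherence {11c}: "Surveys can be returned in person, by mail via a pre-paid envelope, or scanned and emailed to the coordinator". Retention section {18b} asks for return once the week of dressing changes is over, and then: "Additional reminder calls will be made once per week for up to 3 weeks to encourage the return of surveys".
- **Calls during the week.** Section {18b} has VR families "receive a check-in phone call on the next business day following recruitment to ensure there were no technological issues". All families get a reminder call before the next clinic appointment, or at day 7 if they are not coming back to clinic.
- **Reporting.** Section {22}: "Study coordinators will carefully review collected data for any adverse events reported during the study intervention and immediately report this information to the project manager". It also requires serious events to go to the sponsor and IRB without delay, and gives every participant a coordinator's direct number for reporting adverse events.

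**The concern.** The questions that ask about sickness are answered at home during the week, but staff are not due to see the answers until the week is over. A solicited report will therefore usually be read after the last headset session. The calls that fall inside or just after that week have stated purposes of checking the technology and encouraging survey return. None is described as asking how the child tolerated the headset.

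Two things are at stake. The first is timeliness: while the child is still using the headset, staff learn of an event only if the family chooses to phone. The second is completeness. Section {11b} names withdrawal as one option after headset sickness, and a family that withdraws and returns nothing contributes no solicited harms data. Adverse effects of VR are part of the planned secondary analysis under Aim 1, and the Dissemination plans and Discussion look to a toolkit and wider rollout. The tolerability figure will be used, so its denominator matters.

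**Working it through.** **1. The plan's own figure.** Sample size {14} inflates 89 per group for 10% dropout: 89 / (1 − 0.10) = 98.9, rounded up to 99, and 100 are planned. This reproduces. The article gives no survey-return rate and no simulator-sickness rate. Using the dropout allowance as the non-return rate is an assumption: 0.10 × 100 = 10 VR children without solicited harms data.

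**2. Delay by the survey route.** Inputs: an event on day 1; planned return at about day 7 (Table 1 and section {18b}); weekly reminders for up to 3 further weeks, counted from day 7.

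- Planned return: 7 − 1 = 6 days.
- Return at the last reminder: 7 + 21 − 1 = 27 days.
- Phone line: no built-in delay, but it depends on the family calling.

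**3. Share of affected children missed.** Let m be the proportion not returning surveys, r the event rate in non-returners divided by that in returners, and f the fraction of affected non-returners who phone. Then

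missed share = m·r·(1 − f) / [(1 − m) + m·r].

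For m = 0.10, r = 2, f = 0: 0.20 / (0.90 + 0.20) = 0.18. The values of r and f, and m above 0.10, are assumptions.

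| m | f | r = 1 | r = 2 | r = 3 |
|---|---|---|---|---|
| 0.10 | 0 | 10% | 18% | 25% |
| 0.10 | 0.5 | 5% | 9% | 13% |
| 0.20 | 0 | 20% | 33% | 43% |
| 0.30 | 0 | 30% | 46% | 56% |

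If every affected non-returner phones (f = 1), nothing is missed in any row.

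**4. Effect on the percentage.** Suppose 10% of returners report sickness and m = 0.10. The percentage in all VR children is 0.90 × 10% + 0.10 × (10% × r), that is 10%, 11% or 12% for r = 1, 2 or 3. The survey percentage among returners stays at 10% throughout. With equal rates the count is low but the percentage is unbiased; it is too low only when non-returners are sick more often.

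**The case against.** The strongest reply is that the plan does have a real-time route that does not depend on survey return. Every participant gets a coordinator's number for adverse events. Families are told at recruitment which symptoms to watch for and that the headset can come off. Children with a history of motion sickness, seizure disorder or dizziness are excluded, and the IRB deemed the study minimal-risk. The caregiver survey also records time played and interruptions and has a comment section, so staff would not rely on the child's answer alone. The $25 payment favours return, and affected children may continue the surveys without the headset. An article prints no call scripts, so the coordinators may already ask about symptoms.

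Most of this stands, and it rules out three stronger readings that a reader might infer:

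- *That events are captured only from families who return surveys.* The phone line contradicts this. What is true is that events are solicited only through the surveys.
- *That the plan cannot keep its promise of immediate reporting.* In section {22} that word governs two staff steps, coordinator to project manager after reviewing the data, and serious events to sponsor and IRB. No interval from onset is promised, so a 6- or 27-day survey delay breaks nothing stated.
- *That simulator sickness will be undercounted, or that staff are barred from clarifying an event.* The first depends on rates that the documents do not give. For the second, Confidentiality {27} says "The study team has no plans to contact the subjects after their study participation", which concerns contact after participation ends and does not address following up a reported event.

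The reply does not remove the narrower point. The article does state what the calls are for, and asking about adverse events is not among the purposes given. A volunteered report is also no substitute for a solicited one in the families who have stopped responding.

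**Conclusion.** The point holds in a limited form. Followed as written, the plan gives solicited harms data that are normally seen after exposure has ended, and none for families who return nothing. The delay for a day-1 event is about 6 to 27 days, assuming return at about day 7 or at the last weekly reminder.

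Any bias in the sickness percentage is a risk and not a shown result. At 10% non-return with no phone reports, 10% of affected children are missed if rates are equal, and 18% to 25% if non-returners have two to three times the rate. Phone reports reduce these figures, to zero if every affected family calls. The withdrawal option in section {11b} makes a link between sickness and non-return plausible, but the documents do not establish one. The point is worth making because the calls are already planned and recruitment is expected to run to 2027, so later participants can still benefit.

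**What to change.** On the calls already planned in section {18b} (next-business-day VR check-in, pre-visit or day-7 reminder, weekly reminders), ask VR-group caregivers whether the child felt unwell with the headset, and whether and why its use was stopped. The weekly reminders are the most useful for completeness, because they go to the families whose surveys are outstanding. Log the answer in REDCap the same day, pass it through the reporting steps in section {22}, and keep it even if surveys are never returned.

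Confirm that the check-in call goes to every VR family; the sentence in {18b} can be read as covering only those who download the app at home.

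Report harms with the denominator stated (VR children with a survey or a call), and show survey-reported and call-reported events separately.

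Cost: a line in the call script, one REDCap field, about a minute per call and a minor IRB amendment, with no new staff provided the check-in already reaches all VR families. The drawbacks are two sources of adverse event data to reconcile and possibly more events recorded. No clinical rule changes.
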